#### **4. HYPOTHESIS**

- The use of a digital medication event reminder and monitor device-observed self-administered therapy provides a non-inferior medication adherence and treatment outcomes for patients with TB compared with the standard in-person DOT in Ethiopia, one of the low-income countries with the highest burden of TB

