#### **8.5.1.5. Sampling and sample size**

The sample size is calculated considering a 1-sided type I error of 2.5%, a power of 80%, 10% attrition rate, delta of 20%, non-inferiority margin, and a continuous outcome of percentage adherence over the two-month intensive phase, with a standard deviation of 36% and 79% of average adherence, assuming null hypothesis for both arms. The results yield a sample size of 57 in each arm for a total of 114 participants. We will do a  $\log_{10}$  transformation on the data, where a difference can be equivalently transformed into a ratio using a power ( $10^3$ ). The non-inferiority will be calculated as the log in the control minus the log in the intervention, which is equivalent to the log of the control divided by intervention.

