### **8.6. Interventions**

Participants in the intervention arm will receive a 15-days TB medication supply (HRZE fixed-dose combination therapy of 15 doses) in an electronic pillbox device (evriMed500 digital medication monitoring and reminder device manufactured by Wisepill Technologies, South Africa) to self-administer. Providers will collect baseline data, including demographic, socioeconomic, behavioral, and social factors using the study's baseline questionnaire. Based on the baseline data, participants will be clustered into four behavioral determinants (use cigarettes, alcohol, Khat - a psychostimulant plant, and cocaine/marijuana) and three social determinants (homeless, unemployed, and illiterate) as appropriate for the purpose of analysis. Participants in this arm will return every 15 days, where the provider will count any remaining tablets in the pillbox, download the pill-taking data from the Wisepill device, evaluate the functionality of the device and troubleshoot as needed, and perform the urine

isoniazid test. The level of adherence in their intensive phase of treatment will be calculated using the medication possession ratio (MPR). Any participant who misses more than five tablets in any 15- day refills will be reassigned to daily DOT throughout the remaining days of the intensive phase. Participants in the intervention arm can consult the healthcare provider in cases of medical illness or any adverse events outside of a scheduled visit before the next appointment. The phone number of the healthcare provider following their TB condition will be written at the backside of their appointment cards. The phone call strategy aims to maintain the DOT advantage for the intervention arm.

Participants in the control arm will get their treatment as per the standard practice of DOT, where participants will visit the healthcare facility each business day throughout the two months intensive phase to swallow their daily dose of HRZE with direct observation by the healthcare provider. Additionally, they will be given pills for the weekend to take them at home. The provider will collect baseline data, conduct a urine isoniazid test every 15-days, and cluster participants into behavioral and social determinants as applicable for participants in the intervention arm. For this arm, the management of participants who interrupt treatment will follow the national TB treatment guidelines.

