## **8.7. Study procedure**

The main data collection tools will include

- a baseline patient information questionnaire (demographic, socioeconomic, behavioral, social, and clinical information),
- medication adherence measurement tools (MERM vs. DOT daily treatment adherence monitoring tool and urine colorimetric isoniazid test - IsoScreen™ test, GFC Diagnostics Ltd, Bicester, England, and adherence self-report questionnaire),
- clinical measurement tools (pre-post treatment sputum Xpert MTB/RIF assay or microscopy and adverse treatment outcome monitoring tool),
- cost/economic tools (health-related quality of life [HRQoL], catastrophic cost, post-diagnostic cost from an individual patient's perspective, predictors of HRQoL and catastrophic costs,

- Usability and treatment satisfaction tools (treatment satisfaction questionnaire for medication version 1.4 (TSQM v1.4) tool and an 18-item treatment satisfaction questionnaire)

The study investigators will identify healthcare providers in the TB clinics and provide training on the study procedures, how to operate the evriMED500 device, and perform a urine isoniazid test. The investigators will perform a 1:1 randomization of participants before the start of the study using computer-generated random numbers. Providers will enroll participants in the two arms sequentially as they arrive in the clinic and the investigators will routinely monitor the process. Providers will provide instruction using the Amharic version of the study's participant information sheet. Providers will recruit participants and obtain written informed consent in the local language, which is Amharic. The consent form will also function as an acknowledgment of personal responsibility keeping the device properly and returning upon completion of the study.

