## **9. STATISTICAL ANALYSIS**

Descriptive summary measures will be used to report participant characteristics. Chi-square tests will be used to evaluate potential associations among categorical variables. To compare the level of adherence between study arms and among variables, independent t-tests will be done on log-

transformed adherence percentage of the expected 60 days. Effects of the arms and other adherence variables will be estimated using a geometric mean (GM) with geometric standard deviation (GSD) and mean ratios (MR) with 95% confidence intervals (CI). Log binomial regression will be conducted to identify risk factors of at least one negative isoniazid urine test and self-reported adherence of participants. Effects will be measured using adjusted relative risk (ARR) with 95%CI. A general linear model will be done on log-transformed adherence percentage to identify the effects of variables on participants' level of adherence. Effects will be measured using an adjusted mean ratio (AMR) with 95% CI.

Descriptive statistics including frequency and percentage will be used to describe the health state of the study participants. Multiple bar charts with cross-tabulation will be used to illustrate distributions of health states by study arms. Chi-square and Fisher's exact tests will be employed to compare the five EQ-5D-5L health domains by study arms. Kolmogorov–Smirnov, Shapiro–Wilk tests, and median values with interquartile range (IQR) will be used to summarize EQ-5D-5L index value/utility. Nonparametric Mann–Whitney U test will be employed to compare the difference in EQ-5D-5L index value/utility among study arms. A log-binomial model will be used to identify risk factors for lower HRQoL, which is having at least one health problem.

The overall TB treatment cost will be estimated by considering costs related to anti-TB drug pick-up, guardian costs, and coping costs over the two-month intensive phase. The proportion of study participants who faced catastrophic costs at a cut-off point of 20% will be estimated. A cross-tabulation will be employed to evaluate the distribution of catastrophic cost over the study arms and chi-square test will be used to test the association between catastrophic cost and study arms.

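### Poor adherers in the MERM arm are moved to daily DOT, but the protocol does not fix how their later days count in a non-inferiority claim about self-administered therapy

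*Protocol*

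**What the plan says.** Section 4 states the hypothesis that "device-observed self-administered therapy provides a non-inferior medication adherence", with the same claim for treatment outcomes, compared with in-person DOT.

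Section 8.6 sets a trigger in the intervention arm only. A participant who misses more than five tablets in any 15-day refill "will be reassigned to daily DOT throughout the remaining days of the intensive phase". Control participants who interrupt treatment are managed under the national guidelines, so the move goes one way, from the tested strategy to the comparator.

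Section 6.1.1 defines the first primary outcome as each person's percentage adherence over the two-month intensive phase, compiled from MERM device records in one arm and DOT records in the other. Section 8.6 adds that adherence is calculated as a medication possession ratio. Section 9 compares the arms by t-test on the log-"transformed adherence percentage of the expected 60 days". The second primary outcome (Section 6.1.2) is smear conversion after the two months, so it is also read after any period on DOT.

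None of these sections cuts off follow-up at reassignment or says whether doses taken after it belong to the MERM arm.

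**The concern.** Reassignment is triggered by low adherence, which is itself the primary endpoint, and its consequence is the comparator treatment. The worse self-administration performs, the more of the intervention arm's 60 days are spent on DOT, and the more alike the two arms become. In a superiority trial that would make the test conservative. In a non-inferiority trial it makes a false claim easier.

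Three ways of handling reassigned participants lean toward non-inferiority: crediting their DOT doses to MERM, excluding them, or counting them as control. A fourth, counting only device records so that later days score zero, leans the other way. The protocol does not choose, so the same data could support opposite conclusions, and the choice could be made after adherence has been seen.

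**Working it through.** **1. The plan's own figure.** Section 8.5.1.5 gives a one-sided type I error of 2.5%, "a power of 80%, 10% attrition rate, delta of 20%, non-inferiority margin", and a continuous outcome "with a standard deviation of 36% and 79% of average adherence", with no true difference.

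- n per arm = 2 × [36 × (1.960 + 0.842) / 20]² = 50.9, rounded up to 51.
- With 10% attrition: 51 / 0.9 = 56.7, rounded up to 57 per arm, 114 in total.

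This reproduces the stated size. The checks below use 51 evaluable per arm and the raw percentage scale, because no ratio margin is stated for the log scale.

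**2. Simple case, doses credited to MERM.** Assume that a share p is reassigned after the first 15-day window, with 50% adherence before and 79% on DOT. The 79% is the planning mean. The 50% and p are assumptions.

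- Shift in arm mean = p × (45/60) × (79 − 50).
- p = 0.20: 4.35 points. p = 0.30: 6.5 points.
- Standard error = 36 × √(2/51) = 7.13.
- False non-inferiority rate at a true 20-point deficit = 1 − Φ(1.96 − shift/7.13).
- p = 0.20: 1 − Φ(1.35) = 0.089. p = 0.30: 1 − Φ(1.04) = 0.148. The nominal rate is 0.025.
- If DOT adherence were 95% instead of 79%, 30% reassigned would shift the mean by 0.30 × 0.75 × 45 = 10.1 points.

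**3. Simulation of the rule itself.** Control mean 79%, self-administered mean 59% (a deficit equal to the margin), SD 36, beta-distributed individual adherence with a constant daily probability, four windows of 15 doses, a switch when more than five are missed, and tablets read as daily doses. About 54% are reassigned with days remaining. A two-sample test against the 20-point margin gives:

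| Adherence of reassigned participants on DOT | MERM arm mean | Chance of declaring non-inferiority |
|---|---|---|
| No reassignment | 59% | about 2% |
| at least 60% | about 71% | about 55% |
| at least 70% | about 75% | about 84% |
| at least 79% | about 78% | about 97% |

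These rates let the SD vary. Switching shrinks the SD in the MERM arm (to about 18 and 15 in the last two rows), so holding it at 36 would understate the effect.

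**4. Other readings.**

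- Reassigned participants excluded: the remaining MERM mean in the same scenario is about 93%, again favouring non-inferiority.
- Only device records count, later days score zero: with equal true adherence of 79% and SD 36, power falls from about 79% to 59%. The bias is now against MERM.

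**5. Smear conversion.** It is exposed to the same switch. The only margin in the protocol is for percentage adherence, so no error rate can be computed for conversion.

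**The case against.** A reader might infer that the protocol counts DOT-supervised doses toward the MERM arm and is therefore biased toward non-inferiority. The text does not go that far. Crediting is the natural reading of a 60-day comparison by arm, but the outcome is drawn from device records in one arm and DOT records in the other, and the device-only reading reverses the direction. This objection stands, and the point is conditional for that reason.

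A second objection is that counting all 60 days as randomised is legitimate if the target is the whole strategy, MERM with fallback to DOT. Section 8.2 describes an effectiveness-implementation hybrid, and Section 7 looks to scale-up. That is fair, but Section 4 makes its claim about self-administered therapy, so either the claim or the analysis has to change.

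Third, analysis sets and treatment switching are often left to a statistical analysis plan, which may exist. This stands only in part. The hypothesis, the outcome window and the 60-day denominator are fixed in the protocol and do not match one another. Section 8.7 also plans a separate analysis for the mirror case, self-administered doses in the control arm.

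Finally, the sizes rest on assumptions. No document figure gives the share reassigned or adherence after reassignment. The simulated population is U-shaped, with over half reassigned. If poor adherers stay poor on DOT, the effect shrinks. This stands: the figures show what is possible and are not forecasts.

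**Conclusion.** The concern holds in conditional form. The protocol moves poor adherers to the control treatment, compares arms over the full two months without a cut-off, and makes its claim about self-administered therapy, without fixing how post-reassignment days count. If those days are credited to MERM, or reassigned participants are excluded or counted as control, inferiority of self-administration can be masked. If later days score zero, MERM is penalised.

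Under the modest assumptions, the false-claim rate rises from 2.5% to about 9% to 15%. Under the planning SD with a beta distribution, it reaches about 55% to 97%. Both ranges depend on the assumed share reassigned (set by the beta shape in the second), the assumed adherence on DOT, tablets read as daily doses, and the raw scale in place of the planned log scale. If a daily dose is more than one tablet, more participants would meet the trigger. The documents do not support a firm statement that the trial is biased in one direction, or any error rate for smear conversion. No judgement is made on the reassignment rule as care.

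**What to change.** Leave the reassignment rule as it stands and settle the analysis:

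1. Analyse every participant in the arm to which they were randomised.
2. State that the 60-day analysis counts both device-recorded and DOT-recorded doses, and describe its conclusion as non-inferiority of MERM with fallback to DOT.
3. Add an analysis that scores each window after reassignment at the participant's own self-administered adherence, for example that of the last self-administered window. Claim non-inferiority of self-administered therapy itself only if this analysis also excludes the margin.
4. Report the proportion reassigned.

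In the scenario of the simulation, the scoring in item 3 brings the false-claim rate to about 1.5%. It is slightly conservative, because the window carried forward is the one that triggered the switch; it lowered the arm mean by about 0.2 to 2.5 points across the runs. Requiring both analyses is one defensible repair. Restricting the hypothesis and conclusions to the fallback strategy would be another.

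The cost is wording and one extra analysis of data already recorded, with no additional participants. The downside is that a claim about self-administration becomes somewhat harder to reach.

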## **8.7. Study procedure**

The main data collection tools will include

- a baseline patient information questionnaire (demographic, socioeconomic, behavioral, social, and clinical information),
- medication adherence measurement tools (MERM vs. DOT daily treatment adherence monitoring tool and urine colorimetric isoniazid test - IsoScreen™ test, GFC Diagnostics Ltd, Bicester, England, and adherence self-report questionnaire),
- clinical measurement tools (pre-post treatment sputum Xpert MTB/RIF assay or microscopy and adverse treatment outcome monitoring tool),
- cost/economic tools (health-related quality of life [HRQoL], catastrophic cost, post-diagnostic cost from an individual patient's perspective, predictors of HRQoL and catastrophic costs,

- Usability and treatment satisfaction tools (treatment satisfaction questionnaire for medication version 1.4 (TSQM v1.4) tool and an 18-item treatment satisfaction questionnaire)

The study investigators will identify healthcare providers in the TB clinics and provide training on the study procedures, how to operate the evriMED500 device, and perform a urine isoniazid test. The investigators will perform a 1:1 randomization of participants before the start of the study using computer-generated random numbers. Providers will enroll participants in the two arms sequentially as they arrive in the clinic and the investigators will routinely monitor the process. Providers will provide instruction using the Amharic version of the study's participant information sheet. Providers will recruit participants and obtain written informed consent in the local language, which is Amharic. The consent form will also function as an acknowledgment of personal responsibility keeping the device properly and returning upon completion of the study.

For both arms, the providers will collect baseline data, including demographic, socioeconomic, behavioral, and social determinants social using the study's baseline questionnaire. For participants in the intervention arm, the providers will orient participants in the intervention arm as they enroll about how to use the evriMED500 device. The orientation time will depend on the efficiency of the participants to fully acquire and demonstrate the necessary skills. Providers will then dispense a 15-days TB medication supply (HRZE fixed-dose combination therapy of 15 doses) to participants within the evriMed500 device for self-administration. Providers will collect sputum specimens from participants; write their cell phone numbers at the backside of participants' appointment cards to communicate in cases of medical illness or any adverse events before the next appointment, and inform them to return every 15 days. When participants returned, the providers will count any remaining tablets in the pillbox, download the pill-taking data from the evriMED device, check functionality of the device, and conduct a urine isoniazid test. The providers will fill out the study's adherence follow-up form to capture information if the drugs are taken every day, and if not, the reasons for non-adherence. The providers will then evaluate the level of adherence based on the preset criteria, and refill a 15-day TB medication supply in the same pillbox as appropriate. The providers will collect sputum specimens from participants at the end of the intensive phase.

For the control arm, providers will handle participants according to the standard DOT procedure, where participants will visit the healthcare facility each business day in the intensive phase to swallow their daily dose of HRZE with direct observation by the provider. The providers will fill out a similar adherence follow-up form for the control arm. Additionally, if a participant in the control arm requests medications

for self-administration, the provider will collect information about the date requested and for how many days requested on the follow-up form.

For the control arm, in addition to monitoring medication adherence, a separate secondary analysis will be conducted for any doses that are self-administered after approval from their provider to determine if this approach has an impact on other outcome measures. This will be to determine the real-world practice of in-person DOT where some doses might be self-administered when the provider approved this procedure for extenuating circumstances.

The participants will have IsoScreen™ urine isoniazid test every 15 days, which is a colorimetric assay, whereby the pyridine ring structure of isoniazid and its metabolites is broken by the biochemical reaction leaving it vulnerable to attachment by the condensing agent, barbituric acid.

At the end of the intensive phase, trained research experts will complete several data instruments for all participants. The first is a self-report of medication adherence that the experts will administer. The second is a case report form for which data will be extracted from TB registration logs and participants' charts, focusing on overall treatment outcomes and side effects. For the third instrument, the experts will administer the EuroQol's EQ-5D-5L HRQoL questionnaire to all participants. The experts will also assess patients' costs using the Tool to Estimate Patients' Costs. Then the experts will administer the TSQM version 1.4 tool to determine treatment satisfaction. Finally, the experts will administer the 18-item tool to determine user performance of the MERM device for intervention participants. Following the collection of data from participants, the study investigators will collect qualitative and quantitative data from the providers to learn more about the usability and acceptability of the intervention from providers and the healthcare system perspectives. The investigators will follow-up and capture ongoing data on the status of each pillbox, thus from the distribution of the pillboxes to end of data collection.

For the laboratory research involving biological specimens (urine and sputum), the study will use WHO-approved diagnostic tools. The IsoScreen test is a semi-quantitative urine test that provides a reliable and immediate indication of adherence to isoniazid-containing treatment regimens for patients with TB. It uses the reagents of the Arkansas Method: barbituric acid (20 mg), potassium cyanide (10 mg) and chloramine-T (10 mg), in an enclosed plastic testing device for safe and rapid testing in clinics and patients' homes. A urine sample is added to the plastic testing device. If the sample develops a blue color, it is positive for isoniazid metabolites and is therefore from a patient who is compliant with the treatment. A blue/purple color indicates that the drug was taken within the last 24 hours. A green color

also indicates isoniazid metabolites, but the drug was probably taken about 48 hours ago. If the sample remains yellow, then the patient is not adhering to their daily treatment. The providers will perform this test within the study facilities for both arms every 15 days, thus four times per participant. Sputum specimens collected before and after the intensive phase. Under the routine practice, the sputum samples will be tested for Acid-fast bacilli (AFB) microscopy to check for sputum smear conversion following the intensive phase. Initiation, termination or completion of treatment will rely only on the standard procedures available at the study sites, which could be acid-fast bacilli or Xpert MTB/RIF assay. Thus, the outcomes of the study's laboratory results will not dictate the standard diagnostic or treatment procedures.

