8. Post-diagnostic cost from an individual patient's perspective: Participant's cumulative direct costs (out-of-pocket costs related to anti-TB drug pick-up) and indirect costs (guardian and coping costs) over the two-month intensive phase.
9. Patient-reported treatment satisfaction: Participant's treatment satisfaction measured using the treatment satisfaction questionnaire for medication version 1.4 (TSQM v1.4) tool on a scale from 0 to 100, with a higher score indicating better satisfaction.
10. Patient-reported usability of the MERM device: Participant's experience using the MERM device measured by an 18-item questionnaire and the score transformed into a scale from 0 to 100, with a higher score indicating better usability (Intervention arm only).

**Methods:** *Design:* A multicenter, randomized, controlled, open-label, non-inferiority, effectiveness-implementation type 2 hybrid trial in ten healthcare facilities in Addis Ababa, Ethiopia. The study will not dictate diagnosis and treatment for TB; thus, it will not introduce or use new medications.

*Setting:* The study country is Ethiopia – a high TB-burden, low-income country located in sub-Saharan Africa. In Addis Ababa, a total of 94 public health centers provide TB care and treatment services under the DOT program. This study stratifies the 94 health centers on the bases of the 10 sub-cities where they are located. From each stratified group, one health center with the largest TB client load will be selected, with a total of 10 health centers to be included. Health management information system (HMIS) quarterly data (April 01 - June 30, 2019) taken from the Addis Ababa Regional Health Bureau will be used for the purpose.

*Participants:* The source population will be all new patients with TB symptoms who come to a study site and undergo bacteriological screening during the study period or TB patients bacteriologically confirmed elsewhere and referred to a study site for TB treatment. Inclusion criteria: i) patients with new, or previously treated, bacteriologically-confirmed drug-sensitive pulmonary TB, ii) eligible to start the

standard 6-month first-line anti-TB medication, iii) outpatient status at the time of screening and enrollment, iv) men or women age  $\geq 18$  years, and v) able and willing to provide informed consent. The sample size calculation yields a sample of 57 in each arm for a total of 114 participants.

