**Intervention:** Participants will be randomly assigned (1:1) to receive a 15-day TB medication supply in the evriMED500® MERM device to self-administer and return every 15 days (intervention arm) or the standard in-person DOT (control arm). Both will be followed throughout the standard two-month intensive treatment phase (2RHZE). The MERM device has an electronic module and a medication container that records adherence, stores medication, emits audible and visual on-board alarms to remind patients to take their medications on time and refill, and enables providers to download the data and monitor adherence.

**Study Duration:** The study duration is 12 months from opening enrollment until completion of data analyses. Participant duration is 2 months for each individual participant to complete all visits.

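### The allocation procedure has unblinded treating providers place arrivals in the two arms sequentially, with no concealment step and no stated blocking or stratification by site, so foreknowledge of the arm is not ruled out

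*Protocol*

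**What the plan says.** Protocol section 8.7 gives the allocation procedure in two consecutive sentences: "The investigators will perform a 1:1 randomization of participants before the start of the study using computer-generated random numbers". Then: "Providers will enroll participants in the two arms sequentially as they arrive in the clinic", with routine monitoring by the investigators.

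The enrolling providers have several other roles. In the same section, "Providers will recruit participants and obtain written informed consent in the local language". On adherence at the 15-day returns of the intervention arm: "The providers will then evaluate the level of adherence based on the preset criteria". They also collect baseline data, dispense, count tablets and complete the adherence follow-up form in both arms (sections 8.6 and 8.7). Section 8.5.2.5 plans one enrolled provider per facility, with a reserve.

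The synopsis describes the design as "A multicenter, randomized, controlled, open-label, non-inferiority, effectiveness-implementation type 2 hybrid trial in ten healthcare facilities". Stratification appears only in the choice of health centers by sub-city (section 8.4), not in the randomisation. Section 9 compares adherence between arms by independent t-tests on log-transformed percentages. It adds a general linear model that gives an adjusted mean ratio, without listing covariates.

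**The concern.** The first primary outcome (section 6.1.1) is percentage adherence, which is patient behaviour. A provider who knows the next arm before a patient is committed can influence who enters it, by timing the approach or by how eligibility is judged. Some exclusions in section 8.5.1.3 rest on judgement, such as whether the patient is likely to leave the area before month two or can take part safely. Section 2.1 reports that providers find daily observed therapy hard on patients and see a preference for taking tablets at home, so a motive to steer is plausible. If more reliable patients went to the pillbox arm, a non-inferiority comparison would lean towards a false claim.

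A second, lesser matter is balance within sites. The ten centers differ in load (14 to 53 cases per quarter in Table 3). With one enrolled provider per center, site and provider differences coincide. If the list is not stratified, arms may be uneven within sites, and an analysis without a site term leaves between-site variation in the error.

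**Working it through.** **1. The plan's own figure.** Inputs from section 8.5.1.5: SD 36, margin 20 (read as percentage points), one-sided alpha 2.5%, power 80%, true difference zero, attrition 10%.

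n per arm = 2 × (1.96 + 0.84)² × 36² / 20² ≈ 50.9, rounded up to 51. Then 51 / (1 − 0.10) = 56.7, rounded up to 57, so 114 in total. This matches the protocol, and the present point does not alter it.

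**2. Can the next arm be known?** This depends on how section 8.7 is read.

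| Reading | Next arm known or guessed correctly |
|---|---|
| List visible in the clinic | 100% |
| *Sequentially* means alternation | 100% |
| Hidden, unblocked 57:57 list; provider tracks the whole list and always guesses the arm that is behind | about 55% (20,000 simulated lists) |

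The protocol does not say which reading applies. It names no holder of the list and no central release or envelope. Nor does it put consent and baseline data before the assignment: section 8.6 describes baseline collection within each arm's procedures. Routine monitoring by the investigators is oversight and does not conceal the next assignment. The resulting bias depends on how often steering occurs and how strongly the steered trait predicts adherence, and the protocol gives neither.

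**3. Within-site balance if the list is unstratified.** One random 57:57 list was spread over ten sites, 40,000 runs for each assumption on site size. The assumptions are (a) near-equal sites of 11 or 12, and (b) sites proportional to the Table 3 loads. The loads sum to 322, so the smallest site gets 14/322 × 114 ≈ 5 patients and the largest 53/322 × 114 ≈ 19. A site counts as 70:30 or worse when its larger arm holds at least 70% of its patients.

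| | Equal sites | Proportional to load |
|---|---|---|
| At least one site 70:30 or worse | 83% | 90% |
| Mean number of such sites | 1.7 | 2.0 |
| Median largest within-site difference | 6 patients | 6 patients |
| Some site entirely in one arm | 0.5% | 8% |

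For comparison, with permuted blocks of 4 within site (sizes as in (b), 20,000 runs), no site reached 70:30 and the largest difference was 2 patients.

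**4. The same check under simple randomisation.** With 11 patients at a site, 8:3 or worse has probability 2 × (1 + 11 + 55 + 165)/2048 = 464/2048 = 23%. For 9:2 or worse it is 2 × (1 + 11 + 55)/2048 = 134/2048 = 6.5%, so over ten such sites the chance of at least one is 1 − (1 − 0.065)¹⁰ ≈ 49%. The conclusion on site balance is therefore the same whether the list is simple or fixed at 57:57.

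**The case against.** The strongest reply is that most of this is inferred from silence. Working through a computer-generated list in order of arrival is ordinary practice. Alternation would contradict the computer-generated random numbers in the sentence before. Blocks and strata are often left to an SAP or to operating procedures; sections 10 and 11.3 refer to an operations manual and standard operating procedures, which are not at hand, and the scheme in section 1.2 could not be read. Site lists or blocks would fit the wording of section 8.7 equally well.

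Much of that stands. A reader might infer that the list is unstratified and that providers can foresee the next arm. The protocol states neither, and under a hidden, unblocked list the guess rate is close to chance. A reader might also infer that the arms will differ in overall size: simple randomisation of 114 gives exactly 57/57 only 7.5% of the time and a difference of 10 or more 40% of the time. That holds only for unrestricted randomisation, which the protocol does not state; a list fixed at 57 per arm ends balanced. Nor is site confounded with arm: under individual randomisation, chance imbalance within sites adds variance without systematic bias. The general linear model in section 9 may include site, since its covariates are not named.

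Provider influence on the records is also limited in places. Intervention-arm adherence comes from time-stamped device records (section 8.1), and research experts administer the end-of-phase instruments (section 8.7). That protects measurement, but not the choice of who enters which arm.

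The objection does not remove the concealment point. How assignments are released is trial procedure, which belongs in the protocol. The sentence that describes it leaves enrolment into the arms with the unblinded person who recruits and treats.

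**Conclusion.** The point holds in a limited form. As written, section 8.7 does not rule out that the enrolling provider knows the arm before the patient is committed, and its wording admits two readings under which the arm is fully known. The consequence would be selection bias in a behavioural primary outcome, of a size that the protocol does not allow anyone to compute. The protocol does not show that foreknowledge will occur.

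On site balance the conclusion is conditional. If the list is unstratified, about 83% to 90% of trials would have at least one site at 70:30 or worse. This rests on a 57:57 list and on assumed site sizes, either equal or proportional to the Table 3 loads. The consequence is lost precision. The planned 57 per arm is reproduced and unaffected.

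**What to change.** Replace the sentence on sequential enrolment in section 8.7 with a full allocation procedure:

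- One computer-generated list per site, in permuted blocks of randomly varying size.
- The lists held by a named role outside the clinic, with no access for the enrolling providers.
- Each assignment released by sequentially numbered, opaque, sealed envelope or by central telephone, only after eligibility, written consent and the baseline questionnaire are complete.
- A log of the release time, so that the order can be audited.

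In section 9, name site as a term in the primary adherence model, in place of reliance on the plain t-test.

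The sample size stays at 114. The cost is about 114 envelopes or calls and the site term, which uses nine degrees of freedom for ten sites. The change has to be in place before enrolment opens, because concealment cannot be restored afterwards. If site lists and concealed release already exist in the operations manual, stating them in section 8.7 settles the allocation part at no further cost.
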